### Eligibility and exclusion

All patients presenting at Skåne University Hospital > 17 years old with a Mayo type 2a or 2b olecranon fracture will be eligible for the study. Patients living in our catchment area but who sustain an olecranon fracture outside the area will be eligible for inclusion if treated at our hospital. The exclusion criteria are:Participants unable to participate in follow-up (for example due to active substance use disorder, dementia, inability to communicate or understand the questionnaires (for example not speaking Swedish), or living in other administrative health-care region).Participants unable or unwilling to give informed written consent.Participants where non-operative treatment is indicated (for example frail patients).Participants with severe open fractures of Gustilo-Anderson type III.Participants with pathological fractures.Participants that are treated with surgery later than 14 days from the initial trauma.Participants operated by a surgeon who has not attended education on the present study and surgical methods provided by the study officials. If surgery is supervised by a surgeon that has attended the education, the participant will not be excluded.

If a participant meets any of the exclusion criteria, the study officials will exclude them from the study. An anonymous record of the number of eligible but excluded participant, including reason for exclusion, will be kept by the study officials.

### Enrolment and consent

Eligible participants will be identified at the emergency department by the initially treating physician or by any treating physician or steering committee at any time point prior to intervention. Upon identification, potential participants will receive consent forms, written and oral information about the study from the steering committee. Participation is voluntary and participants will be required to sign a written consent form. Participants who decline participation will receive treatment according to the treating physicians’ preferences. The exclusion criteria include inability to understand the given information or written consent. Thus, no consent will be presumed. Recruitment will end when 200 participants are included.

### Allocation and randomization

Prior to commencement of the study, a randomization sequence will be created by a research assistant using a tool provided by the US National Cancer Institute (NCI) [43]. The sequence will be created using maximally tolerated-imbalance (MTI) randomization and entered into the REDCap software [44, 45]. No one will be able to access the sequence once entered to into REDCap. Randomization will be stratified by age (≥ 65 years/ < 65 years), gender (male/female), and smoking (yes/no). These parameters are chosen as they are hypothesized to affect outcome and are available at inclusion.

Before the intervention, stratification data will be collected and the participant will be allocated to either intervention in the surgical ward just prior to when the patient enters the operating theatre by the steering committee using the sequence in the REDCap software, whereby a unique ID will be created for each participant.

### Blinding

Study participants will not be actively informed about which method was used but will be informed upon request. The physiotherapists measuring outcomes during follow-up will not be blinded to the treatment method; as they have access to the hospital files, a reliable blinding will be impossible to achieve in a cost-effective way. The physician assessing secondary dislocation or nonunion cannot be blinded as the treatment method will become apparent in the radiograph analysis. The study officials, surgeons, and other health-care providers will not be blinded. Data analysis will be performed on a blinded data set.

### Intervention

Intervention is internal fixation by either CF or TBW in the corresponding study arms. All orthopaedic surgeons subspecialized in trauma at our department are familiar with both treatment methods and have attended an education organized by the study officials. Surgery may be performed by other surgeons if supervised by a surgeon who has attended the education. During the trial, no specific concomitant treatment is prohibited or controlled by the trial.

#### Intra-operative standards

All participants will receive prophylactic intravenous antibiotics as a single dose of 2 g cloxacillin (or 600 mg clindamycin if allergic to cloxacillin) 30 min prior to the surgery. Tourniquet, fracture forceps, provisional K-wires, and intra-operative fluoroscopy may be used at the surgeons' discretion. A straight, or slightly curved, dorsal approach to the olecranon will be used. Following fracture reduction and fixation, the stability of the fixation will be checked under fluoroscopy during elbow extension and flexion. In case of comminution of the proximal fragment, a supplementary tendon suture may be used to decrease the risk of secondary displacement with implant cut-out. The wound will be closed in layers, and dressings and an elbow cast splint will be applied.

#### Cerclage fixation

The distal fragment will be drilled transversely using a 2.0-mm drill approximately 4 cm distally to the fracture line and 5 mm anterior to the posterior cortex. A cerclage will be put through the triceps tendon, just proximal to its attachment on the olecranon, passed over the fracture in a figure of eight configuration and through the drilled hole, and tightened. A second hole will be drilled at least 10 mm distal to the first hole and a cerclage will be placed through the second hole and the triceps attachment in a figure of zero figuration. Fluoroscopic images of CF are shown in Fig. 1.

**Fig. 1 Fig1:**
[figure not shown]
Fluoroscopy views of olecranon fractures. **A**, **B** Radiographs of olecranon type 2a fractures with a lateral (**A**) and an anterior–posterior view (**B**). Figure 1C and 1D shows radiographs following CF with a lateral (**C**) and an anterior–posterior view (**D**). **E**, **F** Radiographs following TBW with a lateral (**E**) and an anteriorposterior view (**F**)

#### Tension band wiring

The standard TBW method described in the AO guidelines will be used [46]. Fluoroscopic images of CF are shown in Fig. 1.

### Follow-up

After surgery, follow-up will be identical in both study groups (Table 2). Standard peri-operative care will be given at the hospital.

**Table 2 Tab2:** Time-points for follow-up and data gathering, SPIRIT-figure

Activity	− 0.5 to 0	0	0.5	1.5	3	6	12	36
Inclusion, allocation, and randomization	x							
Intervention, both arms	x							
Primary outcome measures								
Reoperation rate				x	x		x	x
Secondary outcome measures								
Complication rate				x	x		x	x
Severe complication rate				x	x		x	x
QuickDASH				x	x		x	x
Patient satisfaction				x	x		x	x
Pain at rest				x	x		x	x
Pain in motion				x	x		x	x
SMFA		x					x	
Tertiary outcome measures								
ROM, flexion			x	x	x		x	x
Grip strength			x	x	x		x	x
Post-operative antibiotics				x	x		x	x
Secondary non union^a^			(x)	(x)	(x)	x	(x)	(x)
Sick leave				x	x		x	x
Fluoroscopy time		x						
Fluoroscopy DAP		x						
Operation time		x						

^a^The secondary dislocation or nonunion rate will be assessed from a lateral elbow radiograph at 6 months or will be recorded if diagnosed at any other time-point

In addition to descriptive baseline data, operation time, fluoroscopy DAP, and fluoroscopy time will be recorded. SMFA-questionnaires will be administered and collected by The Swedish Fracture Register (SFR) by mail shortly after the trauma (recall of pre-injury status), and 12 months later, and this data will be retrieved from SFR by the study officials.

At 2 weeks post-operatively, the cast will be removed, and a physiotherapist will record grip strength and ROM. Any reoperations, complications, ROM, grip strength, and return to work will be recorded at 6 weeks, 3 months, 12 months, and 36 months at the outpatient clinic at the dept. of Orthopaedics by a physiotherapist. PROMs (except SMFA) will be recorded by the participants in REDCap at the same time points. Reoperations and complications are recorded in each patient’s medical journal and subsequently retrieved by the study officials at interim analysis points and at the end of the trial.

At 6 months, a lateral view radiograph will be assessed by researchers DW and GC for any secondary dislocation or non-union. If secondary dislocation or nonunion is confirmed at any other point during the study, it will be recorded.

Any issue requiring additional follow-up or treatment will be handled in the standard health-care system which is public and tax-financed. After 36 months, the current follow-up will end.

### Post-inclusion withdrawals and exclusions

Participants included during the initial assessment may be excluded at any point post-inclusion if exclusion criteria are met. If consent has been given at this point, the data already recorded will be analysed. Participants may decide to voluntarily withdraw at any point, receiving standard healthcare. Upon withdrawal, participants may choose to allow previously and future health-care data to be analysed, only allow previously collected data to be analysed, or decline analysis of any such data.

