### Sample size

The primary outcome measure of the study is reoperation rates, and the sample size is based on this metric. Reoperation rates are assumed to be 13% for CF and 27% for TBW, based on a previous study at our institution [16]. As active patient participation is not required to calculate reoperation rates, and as it will be collected in the same health-care system as the previous retrospective study, we do not expect any drop-out of participants (relative to that study) for assessment of reoperations. The sample size of each arm needed to achieve 80% power is 98; thus, we plan to recruit a total of 200 participants, yielding 81% power.

We expect all 200 participants to be available for analyses of peri-operatively recorded variables (age, sex, fracture type, fluoroscopy DAP, fluoroscopy time and operation time). For analyses of complications, the same assumption is made as for reoperations, i.e. no drop-out relative to our previous retrospective study. For all other variables collected at follow-up, we expect 170 participants to be available for statistical analysis. The expected power for all variables at different sample sizes are shown in Table 1, including all relevant assumptions made.

**Table 1 Tab1:** Statistical power and sample size requirements for study outcomes

	**Power *****n***** = 200**	**Power *****n***** = 170**	***n***** needed for 80% power**	**MDD *****n***** = 100**	**MDD**	**MDD *****n***** = 170**	**MDD**	**x̄ or proportion**	**SD**	**MCID**

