### Statistical analysis

For power and sample size calculations, the alpha value was set to 0.05. Our hypothesis is that CF will yield lower reoperation and complication rates, lower intra-operative radiation, and less intra-operative fluoroscopy time; thus, one-sided tests of proportions were used for sample size requirements calculations [47]. For all other variables, tests for non-inferiority were used with assumed means for ratio scalar and interval variables and assumed proportions for nominal variables [47].

Statistical power and sample size requirements for demonstrating clinically significant differences between the groups were calculated using minimal clinically important difference (MCID) values from the literature. Power and sample size data, including relevant assumptions for all calculations, are presented in Table 1.

We expect ≥ 80% power for reoperation rates, complication rates, severe complication rates, *Quick*DASH, SMFA, patient satisfaction, pain in motion and at rest, and ROM. However, we do not expect to achieve 80% power for analysis of grip strength, postoperative antibiotics use, secondary dislocation or nonunion rate, sick-leave time, fluoroscopy time, fluoroscopy DAP, or operation time (Table 1).

The minimal detectable differences (MDD) for various outcomes and study sizes are presented in Table 1. For some of the secondary and tertiary outcome measures, the MDD is smaller than the MCID meaning that the study is under-powered for proving non-inferiority between the groups. Early termination of the trial resulting in a smaller sample size would further reduce MDD, hampering the power of the study.

The final study groups consist of all participants that complete the follow-up and participants that withdraw but permit analysis; see the section “ Post-inclusion withdrawals and exclusions”. The study groups will be compared using the chi-squared test for categorical variables (reoperation, complication) and Student’s *t*-test for continuous variables.

Comparisons between the study groups will primarily be performed by “intention to treat” analyses. If large cross-over between study groups occurs, “as treated” analyses will be performed as well. Subgroup analysis stratified by Mayo classification, age, gender, open fracture, and high energy trauma is planned for all outcomes.

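### Participants excluded after randomisation have their reoperation data cut off at exclusion without need, and the data kept under the middle withdrawal option are not defined by event date

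*Protocol article*

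**What the plan says.** All places are in the protocol article.

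- *Post-inclusion withdrawals and exclusions*: a participant who meets an exclusion criterion may be excluded at any time after inclusion. For that person, "If consent has been given at this point, the data already recorded will be analysed". A participant who withdraws has three choices. The first releases past and future health-care data. The other two are to "only allow previously collected data to be analysed, or decline analysis of any such data". The choices are attached to withdrawal only.
- *End of trial and early termination*: the study ends when every recruited participant has completed follow-up, been excluded or withdrawn. Exclusion is thus an end state for follow-up.
- *Sample size*: reoperation rates can be calculated without active participation, and "we do not expect any drop-out of participants (relative to that study) for assessment of reoperations".
- *Follow-up*: the physiotherapist records reoperations at 6 weeks and at 3, 12 and 36 months. They also stand in the medical journal and are "subsequently retrieved by the study officials at interim analysis points and at the end of the trial".
- *Statistical analysis*: comparisons are primarily by intention to treat.

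**The concern.** Reoperation is an outcome that a hospital record can supply whether or not the patient attends. The plan relies on this when it allows for no drop-out. The exclusion rule gives that advantage away. Once a randomised participant is excluded, nothing after that date is analysed, and the participant is not asked whether the record may still be used. A rule that stops outcome collection in randomised, consenting participants sits badly with an intention-to-treat primary analysis.

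The withdrawal rule raises a lesser question. Under the middle option the usable data are those already collected. The *Follow-up* section separates an event's entry in the journal from its retrieval by the study. A reoperation that falls between two captures, followed by withdrawal before the next one, may or may not be usable.

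At stake are some primary-outcome events. If losses are related to reoperation itself, the comparison could also be distorted.

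**Working it through.** **1. Who can be excluded after randomisation.** *Allocation and randomization* places allocation just before the patient enters theatre, so most criteria in *Eligibility and exclusion* are settled by then. Two can still arise or come to light later:
- inability to take part in follow-up, for which the examples include dementia, active substance use disorder and living in another health-care region;
- surgery by an untrained and unsupervised surgeon.

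In the second case exclusion comes before any reoperation could occur, so the participant's whole primary outcome would be cut off.

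**2. The rules side by side.**

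| | Data before the cut-off | Data after the cut-off |
|---|---|---|
| Withdrawn, first option | kept | kept (health-care data) |
| Withdrawn, middle option | kept if collected | not used |
| Withdrawn, third option | not used | not used |
| Excluded after consent | kept if recorded | not used, no option offered |

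A consenting participant who is excluded by the study thus has less scope to contribute outcome data than one who chooses to leave.

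**3. The ambiguity before the cut-off.** Take a participant reoperated at month 8 who withdraws at month 10 and chooses the middle option. The event falls between the 3- and 12-month visits. It is in the journal, but the study holds it only if an interim retrieval fell between the two dates. Interim analyses run every 6 months from May 2024. Recruitment began in January 2023, so there is no interim retrieval for about the first 16 months, although visits at 6 weeks, 3 months and 12 months fall inside that period for early recruits.

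**4. The plan's own power.** Inputs:
- "Reoperation rates are assumed to be 13% for CF and 27% for TBW"
- "For power and sample size calculations, the alpha value was set to 0.05"
- "one-sided tests of proportions were used for sample size requirements calculations"
- Stated sample size and power: "The sample size of each arm needed to achieve 80% power is 98; thus, we plan to recruit a total of 200 participants, yielding 81%".

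Unpooled normal approximation:

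n = (1.645 + 0.842)² × (0.13×0.87 + 0.27×0.73) / 0.14² = 6.183 × 0.3102 / 0.0196 = 97.8, so 98 per arm.

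Power at 100 per arm = Φ(0.14/√(0.3102/100) − 1.645) = Φ(0.869) = 80.8%. Both stated figures are reproduced. The pooled form gives 100 per arm and 80.0% power, and is used as the base below.

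**5. Illustration of size.** The documents give no exclusion or withdrawal rate and no share of uncaptured events, so the loss fractions are assumptions. Expected reoperations are 0.27×100 + 0.13×100 = 40.

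(a) A fraction f of reoperations is missed equally in both arms, and those participants are counted as event-free. Both rates become (1 − f) times the planned rate, and

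power = Φ{[Δ√n − 1.645√(2p̄(1−p̄))] / √(p₁q₁ + p₂q₂)}, n = 100.

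| f | Events missed of 40 | Difference, 14(1 − f) points | Power |
|---|---|---|---|
| 0 | 0 | 14.0 | 80.0% |
| 1% | 0.4 | 13.9 | 79.6% |
| 2% | 0.8 | 13.7 | 79.1% |
| 5% | 2 | 13.3 | 77.7% |
| 10% | 4 | 12.6 | 75.3% |

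(b) A fraction of participants drops out of the analysis altogether, equally in both arms, with rates unchanged: 2%, 5% or 10% gives 79.3%, 78.2% or 76.2%.

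**The case against.** The strongest reply is that the wording can be read benignly. The middle option is one of three, and the first keeps everything. Set against future health-care data, previously collected data may simply mean data that predate withdrawal. For exclusions the plan speaks of recorded data, and *Follow-up* says that reoperations are recorded in the journal before the study retrieves them. A reoperation before exclusion may then already qualify. Visits are a second capture route. The text is also a condensed article, and the scope of each option may be spelled out in the full protocol or the withdrawal form.

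Most of this stands for events before the cut-off, which is why that part is only an ambiguity. It does not answer the point about events after exclusion. There the article states a rule, and no reading of recorded data reaches a later reoperation.

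A reader might go further in four ways that the documents do not support:

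- *Withdrawal in general loses earlier reoperations.* Only the middle option is unclear, and only between captures.
- *Retrieval stops when recruitment ends in 2027.* The article gives the interim analyses a start and an interval but no end, so this is an inference.
- *Lost events will be counted as no reoperation.* The article does not say how incomplete outcomes are coded, and an analysis plan commonly settles this. Case (a) assumes it.
- *Power falls by 5 to 16 points.* That needs 10–30% of reoperations, or 4 to 12 of the expected 40, to fall into the gap. Nothing in the documents suggests such a share.

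The no-drop-out statement is also qualified as relative to the earlier retrospective study, so it is not a claim of complete capture.

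**Conclusion.** The point holds for exclusions. As written, the plan discards later reoperations of randomised, consenting participants who are excluded, although the outcome could be read from the record and intention to treat is primary. For withdrawers who take the middle option, the plan is ambiguous about events in the journal that have not yet been captured. This probably affects few people.

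The size cannot be derived from the documents. If 1–2% of reoperations were lost equally in both arms, one-sided power would fall by about one point or less. A loss of 10% would cost about five points. Both figures assume the planned rates, 100 per arm, and missed events counted as non-events. The reason to act is that the loss is avoidable, and that data outside a participant's recorded choice may not be recoverable later.

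**What to change.** In *Post-inclusion withdrawals and exclusions*:

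1. Offer participants excluded after randomisation the same three data options as withdrawers, including release of future health-care data. This is the only part of the change that recovers reoperations after exclusion.
2. Define usable data as all trial and health-care data dated up to withdrawal or exclusion, unless the participant declines all use.
3. State that study officials retrieve reoperations and complications from the record up to that date when a participant leaves, within the consent given.

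Align *End of trial and early termination*, so that exclusion does not end record-based follow-up for those who release future data.

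The cost is an amendment to the protocol and the withdrawal form, with notice to the ethics authority, a registry update and information to affected participants, as the article's amendment section requires. Each case adds one record look-up, done by officials who already retrieve these data. Because recruitment is under way, participants who have already left can be covered only as far as their consent allows. For those now treated in another region, the record may be harder to reach.

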### Adverse event management

Any adverse events will be treated in the standard health-care system. In such cases, there will be no difference to the standard care. All participants are fully insured and entitled to compensation through the Swedish Patient Injury Act, under the same conditions as patients not participating in the study.

### End of trial and early termination

Recruitment will end when 200 participants have been recruited.

Interim analyses will be performed by the data monitoring committee every 6 months, starting in May 2024. All participants that have completed the follow up at 6 weeks be included in the interim analyses. For ethical reasons, the recruitment will be terminated by the steering committee if any of the following criteria is met:A statistically significant difference of ≥ 10% in reoperation rate between the study groupsA statistically significant difference of ≥ 10% in severe complications rate between the study groupsA statistically significant difference of ≥ 20 *Quick*DASH points between the groups at any follow-up time-point

In case of termination of the study, participants that have already been recruited will complete follow-up. The study will end when all recruited participants have completed the follow-up, are excluded, or have otherwise withdrawn from the study.

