### Oversight and monitoring

The principal investigator DW and co-authors GC, IK, and CR coordinate the study at all study centres and meet monthly. The day-to-day management of the study will be performed by the steering committee with support from administrative staff from the standard healthcare system. The surgical methods in this trial have been used extensively at our clinic and are considered low-risk; thus, there is no need for a data monitoring committee. Neither the steering committee, authors, nor the sponsor has any competing interests. No external endpoint adjudication system will be used.

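### Six-monthly looks must end recruitment if any of three criteria is met, with no interim significance level stated, and the article contradicts itself on whether the monitoring committee exists

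*Protocol article*

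**What the plan says.** Under End of trial and early termination, the protocol article schedules the looks: "Interim analyses will be performed by the data monitoring committee every 6 months, starting in May 2024". The data set for each look is set by early follow-up: "All participants that have completed the follow up at 6 weeks be included in the interim analyses". Stopping is mandatory: "the recruitment will be terminated by the steering committee if any of the following criteria is met". There are three criteria, and each combines statistical significance with a minimum size:

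- reoperation rate, at least 10%;
- severe complication rate, at least 10%;
- QuickDASH, at least 20 points at any follow-up visit.

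The section does not say at what level significance is judged. Statistical analysis gives the only alpha in the article: "For power and sample size calculations, the alpha value was set to 0.05". It also states that "one-sided tests of proportions were used for sample size requirements calculations", and for the comparison itself: "The study groups will be compared using the chi-squared test for categorical variables (reoperation, complication) and Student’s *t*-test for continuous variables".

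Patients already recruited complete follow-up after a stop. Oversight and monitoring calls the surgical methods low-risk and concludes: "thus, there is no need for a data monitoring committee".

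**The concern.** A rule that ends recruitment as soon as any of several tests is significant at any of several looks has a false-stopping rate well above the level used for each test. The article fixes the trigger and the looks but not the level. A reader who applies the only alpha available gets an uncorrected repeated test.

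Three things are at stake: a real chance of ending recruitment on noise, some inflation of error in the final comparison because the sample size depends on interim results, and lost power on the primary outcome when the planned effect is real. The Discussion accepts that early stopping costs power, but only for other outcomes.

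The looks are also assigned to a committee that another section says is unnecessary, so it is unclear who sees comparative results.

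**Working it through.** **The plan's own figure.** Sample size assumes: "Reoperation rates are assumed to be 13% for CF and 27% for TBW, based on a previous study at our institution". With unpooled variance and one-sided 0.05:

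- n per arm = (1.645 + 0.842)² × (0.13×0.87 + 0.27×0.73) / 0.14² = 6.18 × 0.310 / 0.0196 ≈ 98, as stated.
- Power at 100 per arm: 0.14 / √(0.310/100) = 2.51; Φ(2.51 − 1.645) ≈ 81%, as stated.
- Two-sided 0.05: Φ(2.51 − 1.96) ≈ 71%.

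The stated 98 and 81% are therefore fixed-sample figures with no allowance for looks.

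**Number and size of looks.** Recruitment began in January 2023 at an expected 50 a year (Trial status). May 2024 is month 16, so looks fall at months 16, 22, 28, 34, 40 and 46. Patients past 6 weeks number about 50/12 × (month − 1.5), or roughly 61, 86, 111, 136, 161 and 186.

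**Does the 10% minimum help?** The smallest difference significant at two-sided 0.05 is 1.96 × √(p(1−p) × 4/n):

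| Pooled rate | n = 61 | n = 186 |
|---|---|---|
| 20% | 20.1% | 11.5% |
| 13% | 16.9% | 9.7% |
| 5% | 10.9% | 6.3% |

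At the planned rates, significance almost always implies more than 10%. The minimum binds only when few events have occurred.

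**Does the 20-point minimum help?** Yes, but not in small samples. At month 16 about 50/12 × 4 ≈ 17 patients, or 8 per arm, have a 12-month visit; at month 40 the same number have a 36-month visit. With SD 22 (Table 1) and 8 per arm, the standard error is 22 × √(2/8) = 11, and significance needs about 2.145 × 11 ≈ 24 points. The 20-point minimum adds nothing there.

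**Simulation under no difference.** Assumptions not in the article: even accrual, no missing data, several event-timing patterns, overlap of reoperations and severe complications from none to complete, and QuickDASH within-patient correlation 0.5-0.6. The criteria were applied as written, at 0.05:

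| Quantity | Result |
|---|---|
| False stop on reoperation | 12-16% |
| False stop on QuickDASH | about 7-8% |
| False stop on any criterion | 19-31% (lowest with complete overlap, highest with little or none) |
| Any criterion, rates tested one-sided at 0.05 | about 23-25% |
| Final two-sided reoperation test, all recruited patients | about 6-8%; up to about 12% if all events fall within 6 weeks |
| Reoperation significant at some look or at the end | about 15-17% |

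A normal approximation for reoperation alone gives 13.5% over the six looks and 14.2% with the final test.

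**Simulation under 13% versus 27%.** With events spread over 12 months and severe complications coinciding with reoperations, recruitment stops in about 74% of trials. Average final size over all trials is about 135, and final two-sided power is about 64% against 71% without the rule. With 70% overlap and a 6-month median time to event, about 82% stop.

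**With p<0.001 on all three criteria.** False stopping falls to roughly 1% or less, final error is about 5%, and a true 13% versus 27% difference stops recruitment in about 17% of trials.

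**The case against.** The strongest reply is that the rule ends recruitment and nothing more. Patients already enrolled are followed to the end and the groups are compared then, so an interim crossing is not a declared result. This stands. A reader might infer that type I error on the primary outcome is tripled; the article does not support that. The 15-17% arises only if a crossing is itself reported as the finding. Nor can that figure be combined with the loss of power:

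- if any look or the final test counts, error is about 16% and power about 78%, a gain;
- if only the final test counts, error is about 6-8% and power about 64%.

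A reader might also infer that any p below 0.05 stops recruitment. The text does not say so. Each criterion has a minimum difference, and 0.05 is carried over from the sample-size paragraph. An analysis plan not shown here could set interim levels, though the stopping rule does not refer to one.

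Stopping is presented as a deliberate ethical choice. Blinding specifies a blinded data set for analysis, and Allocation and randomization says nobody can access the sequence. These limit the harm but do not settle who sees group comparisons: the steering committee allocates patients, holds the data, prepares it before each look and ends recruitment.

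Finally, the 64% and 71% are two-sided, whereas the article's 81% is one-sided. That difference is a separate matter; the drop from 71% to 64% is the part due to the rule.

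**Conclusion.** The point holds as a fault in the stopping rule. The article fixes a mandatory trigger at repeated looks over three criteria without saying what level counts as significant. If that level is 0.05, false stopping of recruitment is about 19-31%. To call it likely would overstate this, but it is four to six times 5%. Inflation of the final reoperation test is modest, at about 6-8% under spread-out event timing. The cost under the planned effect is about 7 points of final two-sided power on the primary outcome, which the Discussion does not acknowledge.

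These sizes rest on 0.05 at each look, six looks, even accrual of 50 a year, and the assumed event timing and overlap. The power figure applies to events spread over 12 months with coinciding severe complications.

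The contradiction over the committee needs no assumption. The documents do not show which section is right.

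**What to change.** In End of trial and early termination:

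- Replace the bare significance condition in all three criteria with a stated interim boundary. One option is p<0.001. Another is an O'Brien-Fleming-type spending boundary; for reoperation alone over six looks and a final test, the two-sided levels are about 0.0002, 0.0014, 0.005, 0.011, 0.020, 0.030 and 0.037. Covering three criteria needs stricter levels than these.
- Keep the 10% and 20-point minimums.
- Set a minimum number per arm with data at a visit before QuickDASH can trigger.
- State that the trial's conclusion rests on the final analysis and not on an interim crossing.

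Reconcile that section with Oversight and monitoring: say whether a data monitoring committee exists, who runs the looks and who sees comparative results.

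The cost is a protocol amendment in wording only. The downside of p<0.001 is that a true difference of the planned size ends recruitment early less often, in about 17% of trials instead of 74%.
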